#### Anthropometric measurements

Height, weight, and abdomen girth will be measured at all outcome measurement sessions by project staff. Weight and height will be measured with the participant standing normally, with feet together and head in the Frankfurt plane, using Seca 700 mechanical balance scales and a Seca 220 measuring rod (Seca GmbH, Hamburg). Participants will be asked to remove their shoes and any heavy personal items/items of clothing for the measurement. Abdomen girth will be measured from as the ellipse projected on the transverse plane using the bilateral iliac crests as antipodal tangents using the Seca 203 measurement tape in accordance with the NIH protocol [37].

#### Other measures

Website usage, engagement, and retention for the Web 1.0 and Web 2.0 intervention groups will be measured using a commonly available web traffic analysis platform (Google analytics) and monitoring of user-generated content. Features monitored will include:

• Number of logins

• Frequency of step log use (and steps logged)

• Use of site stream (status updates, and comments on ‘friends’ stream)

• Page visits

• Goals set

• Time on website

• Number of friends (Web 2.0 only)

• Number of blog posts

In the Control group, logbooks will also be collected to enable comparison in use of common features (e.g., step log, goal setting) between interventions.

Quality of life will be assessed with the RAND 36 item Short Form Health Survey (SF-36) which evaluates 8 health concepts including limitations in physical activities and usual role activities because of health problems, bodily pain, general mental health, and vitality (energy and fatigue). The SF-36 has been validated on Australian populations [51], has demonstrated suitability for use in the general population [52,53], and is associated with the stage of motivational readiness to changes in physical activity [54,55].

Participants’ confidence in their ability to execute tasks and trouble shoot problems with the Internet will be measured using the Internet Self-Efficacy Scale (ISES). The effect of Internet self-efficacy is poorly understood in terms of Internet-delivered PA programs. The ISES uses 8 items assessed on a 7-point likert scale to assess a user’s understanding of Internet hardware and software, confidence in gathering information using the Internet and learning skills to use Internet programs, and ability to troubleshoot and resolve Internet problems. The ISES has shown good reliability and internal consistency [43].

A brief psychosocial questionnaire was used to assess key variables pertinent to follow-up analyses of intervention mediation and moderation. These variables include core constructs from the Transtheoretical Model (TTM [56]), Social Cognitive Theory (SCT [41]), and Theory of Planned Behavior (TPB [40]), and have been constructed to align with the target behaviour of taking 10,000 steps per day. From the TTM, Stages of Change is assessed by whether participants are currently taking 10,000 steps per day; if so how long they have been doing so; if not, whether they intend to, or are preparing or beginning to take 10,000 steps per day. This 6-item Stages of Change measure was modelled on a previously published scale [39]. From SCT, we developed a specific set of 4 items to assess self-efficacy for taking 10,000 steps per day, as well as a set of 10 items to assess self-efficacy to overcome common barriers to taking steps from existing guidelines [42]. A set of 9 items was used collectively to assess agreement with the SCT construct of outcome expectations associated with taking 10,000 steps per day. From TPB, we assessed intention with 2 items, subjective norm with 2 items, perceived behavioural control with 2 items, and attitude with 4 items, all with regard to being physically active at a level of taking 10,000 steps per day. These TPB constructs were tailored to the target behaviour of 10,000 steps per day, based on a set of previously published items [57].

Overall user satisfaction of the assigned intervention will be investigated at all follow-up time points using the System Usability Scale [44].

### Statistical power and sample size

Sample size for the RCT is based on the primary outcome measure, minutes of MVPA, as measured by the ActiGraph accelerometer. A review of web-based PA interventions suggests that studies which do not include aspects of Web 2.0 had a small effect on change in PA status of participants and had a dropout rate of approximately 40% [15]. Given the enhanced effects of the Web 2.0 intervention expected on the PA status of participants, the current study will be powered to detect a small to moderate change in minutes of MVPA. Therefore, to achieve 80% power to detect a small to moderate difference in PA between groups (control/Web 1.0/Web 2.0) at any given time point, approximately 120 participants per group will be required using an alpha level of 0.05. The number of participants per group has been inflated by 40% (n=168/group) to account for participant drop out while retaining adequate power to achieve study aims at 18 months.

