### Participants and recruitment

A total of 504 participants will be recruited for this study across two sites in Australia (South Western Sydney and Central Queensland). The primary means of recruiting participants will be a personalised invitation letter to an extract of randomly selected individuals from the Australian Electoral Commission (AEC) electoral roll. Voting is compulsory for persons aged 18 years and over in Australia and AEC data provides an effective means of sampling the targeted population. Previous research utilising a similar method to recruit participants, but requiring mainly survey-based cohort measurements, reported that between 60 and 70% of individuals invited to a research project using this manner, participated [28,29]. The participant requirements of this research, however, are higher than these other studies, and, thus a response rate of less than 10% is anticipated. Therefore, an extract of 14,000 names and addresses - 7,000 from each of the Federal electoral divisions of Capricornia (Rockhampton, QLD) and Werriwa (South Western Sydney, NSW) - matched by age and gender, was obtained from the AEC electoral roll. A number of other recruitment methods will also be utilised to supplement the primary recruitment method and to recruit a diverse range of participants. These methods include advertising in local print media, calling former research participants who had registered their interest in participating in future research, and messages delivered through university email lists.

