### Statistical analysis

All analyses will follow intention to treat principles. Main comparison between groups will be performed using general linear mixed modelling. The impact of missing data will be addressed using multiple imputation. The sample size is inflated to incorporate the additional uncertainty arising from missing data. All analyses will be conducted using SPSS for Windows (Version 15.0). The level of significance (alpha) will be set at 0.05.

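### The 40% dropout allowance is applied as 120 × 1.40 = 168 per group rather than 120/0.60 = 200, so 168 keeps the required 120 completers only if dropout is at most 28.6%

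*Protocol article*

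**What the plan says.** The section Statistical power and sample size of the protocol article builds the sample size in four steps.

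- The outcome: "Sample size for the RCT is based on the primary outcome measure, minutes of MVPA, as measured by the ActiGraph accelerometer".
- The dropout evidence: a review found that earlier web-based studies without Web 2.0 features "had a dropout rate of approximately 40" per cent.
- The base requirement: "to achieve 80% power to detect a small to moderate difference in PA between groups" at any one time point, "approximately 120 participants per group will be required using an alpha level of 0.05".
- The allowance: "The number of participants per group has been inflated by 40% (n=168/group) to account for participant drop out while retaining adequate power" for the study aims at 18 months.

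The total agrees with this: under Participants and recruitment, "A total of 504 participants will be recruited for this study", which is 3 × 168. Under Statistical analysis the article adds: "The sample size is inflated to incorporate the additional uncertainty arising from missing data". No other dropout rate, and no numeric effect size or SD, appears anywhere in the article.

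**The concern.** The cited dropout rate and the inflation percentage are the same number, and the base of 120 multiplied by 1.40 gives 168 exactly. A dropout rate is a fraction of those randomised, so the allowance has to be made by dividing by the fraction retained. Adding 40% to the required number does not offset a 40% loss from the enlarged number.

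The primary hypothesis covers 3, 12 and 18 months, and power is said to be kept at 18 months, where losses have had longest to accumulate. If losses reach the cited rate, the 18-month comparison has fewer completers than the plan itself says it needs. A null result there could then be read as coming from a trial with 80% power when the design did not secure that.

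**Working it through.** **Inputs from the article:** 120 per group required; power 80%; alpha 0.05; three equal groups; cited dropout about 40%; 168 per group and 504 in total planned.

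**Assumptions needed because the article is silent:** a two-sided test; exactly 80% power at exactly 120 per group; a comparison of completers only.

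**Step 1: reproduce the plan's figure.** 120 × (1 + 0.40) = 168, and 3 × 168 = 504. Both match.

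**Step 2: apply the cited dropout to 168.** 168 × (1 − 0.40) = 100.8, about 101 completers per group. The shortfall is 120 − 100.8 = 19.2, about 19 per group.

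**Step 3: the allowance that would keep 120.** 120/(1 − 0.40) = 200 per group, or 600 in total, which is 96 more than 504.

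**Step 4: the dropout that 168 does cover.** 1 − 120/168 = 0.286, so retention must be at least 71.4%. Steps 1 to 4 do not depend on any effect size.

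**Step 5: back-solve the effect.** With the normal approximation, d = (1.960 + 0.842) × √(2/120) = 0.362. A t-test gives 0.363.

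**Step 6: power with the completers left.** Power = Φ(d × √(n/2) − 1.960). At n = 100.8 this is Φ(0.3617 × √50.4 − 1.960) = Φ(0.608) = 0.728.

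The same check under other standard tests, each calibrated to 80% power at 120 per group:

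| Test | Power at 100.8 per group |
|---|---|
| Two-sided, normal approximation | 72.8% |
| Two-sided t-test | 72.8% (72.9% at 101) |
| Three-group ANOVA (f = 0.164) | 72.2% (72.3% at 101) |
| One-sided | 73.7% |
| Bonferroni for three comparisons | 71.6% |

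The range is about 72–74%, a loss of roughly 6 to 8 points whichever test is assumed.

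**Step 7: difference detectable with 80% power.** (1.960 + 0.842) × √(2/100.8) = 0.395. The t-test at 101 per group gives 0.396, so d rises from about 0.36 to about 0.40.

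**The case against.** Several points on the other side have weight.

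- **A reader might infer that the article promises 80% power after dropout and is simply wrong by seven points.** The 80% is attached to about 120 per group and to an effect described only in words: "the current study will be powered to detect a small to moderate change in minutes of MVPA". For 168 per group at 18 months the article claims only adequate power. A d of 0.40 could carry the same verbal label as 0.36. This limits how firmly any power figure can be stated. It does not rescue the allowance, because 80% is the only power level given and the claim to retain power refers back to it.
- **A reader might take 40% as this trial's forecast.** The article attributes it to earlier studies without Web 2.0 features, and the secondary hypothesis expects better website retention in the Web 2.0 arm. But no lower rate is offered, the allowance uses the same 40%, and the Web 1.0 and control arms lack the Web 2.0 features. The article uses the expected Web 2.0 benefit to support the effect size, not a lower dropout rate.
- **A reader might take 73% as the power of the planned analysis.** It is a completers-only figure. The plan is intention to treat with a mixed model and multiple imputation, and valid baseline ActiGraph data are required before randomisation. If the 120 came from an unadjusted comparison and the model uses baseline, a baseline–outcome correlation of about 0.40 would offset the loss, since 1 − 0.40² = 0.84 = 100.8/120. That correlation is hypothetical. The article neither states one nor derives 168 in this way.
- **A reader might see the missing-data sentence under Statistical analysis as a second use of the same inflation.** It reads more naturally as a restatement of the dropout allowance, so there is no ground for deleting it.

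**Conclusion.** The point stands. The cited 40% dropout is applied by multiplication, and 168 per group leaves about 101 completers at that rate, not the 120 the plan requires. The figure of 168 is sufficient only if dropout is at most 28.6%. These results use only the article's own numbers.

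The power figures rest on more. If 120 per group gives exactly 80% power at two-sided 0.05, completers-only power at 18 months is about 73%, so the chance of missing the target effect is about 27% rather than 20%. The d of about 0.36 is back-solved and is not a design value stated by the sponsor. Any gain from the mixed model or imputation is unquantified in the article. The documents do not support the stronger conclusion that the trial's actual power is known to be 73%, or that more participants must be enrolled.

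**What to change.** Reword the last part of Statistical power and sample size in one of two ways:

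1. State that 504 randomised with 40% dropout gives about 101 completers per group and, on a completers-only basis, about 73% power for the effect that 120 per group would detect with 80% power.
2. State that 80% power at 18 months holds only if retention is at least 71.4% (dropout at most 28.6%), and make that the retention target.

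If a d of 0.36 or 0.40 is printed, label it as back-solved unless the sponsor can supply the effect size and SD originally used. Keep the missing-data sentence under Statistical analysis, but qualify it to say that the inflation covers up to about 29% missing at 18 months.

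The cost is wording only: no added enrolment and no change to conduct or analysis. The downside is that the stated power becomes slightly less favourable.

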### Statistical analysis

All analyses will follow intention to treat principles. Main comparison between groups will be performed using general linear mixed modelling. The impact of missing data will be addressed using multiple imputation. The sample size is inflated to incorporate the additional uncertainty arising from missing data. All analyses will be conducted using SPSS for Windows (Version 15.0). The level of significance (alpha) will be set at 0.05.

## Discussion

The current trial presents a unique opportunity to study the effectiveness of new generation web based applications (Web 2.0) in social marketing and health promotion using a conventional (Web 1.0), established, and ongoing PA promotion program (10,000 Steps Australia) as a comparator. Each year there is a proliferation of health-related and health promotion websites, yet very little work has been carried out to study the utility and effectiveness of these population-targeted websites [58]. Research studying the effectiveness of this now pervasive communication medium has been limited to studies of short duration and at times modestly sized samples [15], with many lacking any comparative study of website components [14]. We expect that the current study’s findings will provide increased understanding of the benefits of new web-based technologies and applications in engaging and retaining participants on web-based intervention sites, with the aim of improved and maintained health outcomes as a result of increased website engagement and retention.

## Abbreviations

AEC: Australian Electoral Commission; ISES: Internet self efficacy survey; MVPA: Moderate-to-vigorous physical activity; PA: Physical activity; PAR-Q: Physical activity readiness questionnaire; RCT: Randomised controlled trial; SCT: Social cognitive theory; SF-36: Short form health survey; TPB: Theory of planned behaviour; TTM: Transtheoretical model.
